### Sample size

We estimated a minimum sample size of 130 volunteers (65 in the placebo group and 65 in the Se group). In this estimate calculation, we considered an α error of 0.05, a β error of 0.20 and a difference in progression risk of 50%. The calculation assumed a progression rate scenario for cardiopathy based on findings for LVEF decline in a previous cohort study conducted in Brazil (Virgem da Lapa, State of Minas Gerais) [44]. See Table 1 for details.

**Table 1 Tab1:** **Minimum sample size estimation**
^**a**^

Parameters	Groups	
	Placebo (***n***= 65)	Selenium (***n***= 65)
Progression rate	54%	27%
Confidence level	95%	95%
Proportion	1:1	1:1

^a^Estimate was calculated with an α error of 0.05, a β error of 0.20 and progression rates in 5 years.

### Randomization

A sequence was computer-generated to randomly allocate 130 patients into 2 groups in a 1:1 ratio. This sequence was generated in blocks of 4, 8 and 12 using the “blockrand” extension of the R Project software package. This sequence is available only to a pharmacist not involved in volunteer recruitment. This pharmacist decided which group would be the placebo group and which would be the intervention group by flipping a coin. Next, opaque boxes will be filled either with placebo or sodium selenite capsules and later sealed and numbered to correspond to the computer-generated sequence. As patients undergo volunteer recruitment by the medical staff, they will be assigned a number sequentially corresponding to a treatment box. Therefore, a strategy of numbered boxes will be used for sequence concealment.

### Blinding

Patients, health-care providers and staff involved in outcome assessment were blinded to treatment. The blinding was conducted using the same strategy of allocation concealment by numbered boxes. Therefore, numbers were assigned to volunteers’ treatments, but only one pharmacist not involved in these tasks will be aware of what is in each numbered box.

### Statistical analysis

The type of analysis of major interest is the intention-to-treat analysis. At baseline, both intervention groups will be compared concerning information that might modify disease prognosis to check if random allocation worked properly at that time. The main analysis will be longitudinal modeling of LVEF by comparing the two intervention groups. This modeling will be conducted with marginal models and conditional models. This analytical strategy will also be used for other continuous outcomes, such as the WHOQOL-Brief.

For each binary outcome of interest, incidence rates will be estimated and compared among the different intervention groups, including the adverse events discriminated by severity and causality. Time-dependent survival models will be adjusted for the binary outcomes, as progression may occur more than once for each participant. The survival modeling extension for multiple events of Prentice, Williams and Peterson will be adopted [45].

Secondary analysis will be conducted as per protocol by adjusted regression. This secondary analysis will be conducted mainly if there is an understanding that random allocation did not fulfill its purposes at baseline.

REDCap software [46] will be used for data management, and data analysis will be conducted with R Project software [47].

### Interim analyses and stopping rules

Four interim analyses are planned. The first will be conducted when the last volunteer completes 6 months of follow-up, the second will be conducted when the last volunteer completes 18 months of follow-up, the third will be conducted when the last volunteer completes 30 months of follow-up and the last will be conducted when the last volunteer completes 42 months of follow-up. Every interim analysis will be submitted for DSMB approval.

Trial interruption for ethical reasons may be recommended by the DSMB and confirmed by the trial coordinators or by the trial coordinators and confirmed by the DSMB. Trial interruption may be recommended due to either positive or negative results exceeding expectations. The prespecified stopping rule is a marginal 10% difference in LVEF among groups, a reduction of progression rate in 50% or more participants observed at the main outcome measurement points, an increase of 10% or more of severe adverse events in one of the intervention groups or serious adverse events in at least 5% of the volunteers. All these estimates should have a significance level of 0.01 or less in any of the interim analyses.

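### The trial coordinators may start a stop on interim results, a role that for most triggers needs between-arm results outside the DSMB and puts blinding and trial conduct at risk

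*Protocol article*

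**What the plan says.** All references are to the protocol article.

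- **Who may propose a stop** (Interim analyses and stopping rules): a stop can be proposed by the DSMB and "confirmed by the trial coordinators or by the trial coordinators and confirmed by the DSMB". There are two routes, and in the second the DSMB confirms rather than originates.
- **Grounds** (same section): the interruption is framed as an ethical one, but "Trial interruption may be recommended due to either positive or negative results exceeding expectations". Efficacy is therefore included.
- **Triggers** (same section): "The prespecified stopping rule is a marginal 10% difference in LVEF among groups", followed by a reduction in progression, an excess of severe adverse events in one group, and a threshold for serious adverse events among volunteers. Then: "All these estimates should have a significance level of 0.01 or less in any of the interim analyses".
- **Number of looks and flow of results** (same section): "Four interim analyses are planned", timed to the last volunteer reaching 6, 18, 30 and 42 months. "Every interim analysis will be submitted for DSMB approval". The preparer is not named.
- **Protocol changes** (Ethical considerations): the protocol may be altered when interim analyses show significant group differences in the primary end point, subject to confirmation from the DSMB, which is described as external.
- **Blinding**: the Blinding section names patients, health-care providers and outcome-assessment staff, and says that "only one pharmacist not involved in these tasks will be aware of what is in each numbered box". The Abstract promises patients and health-care providers five years of blinding.

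**The concern.** A person asked to judge whether a between-arm difference has crossed a threshold must see that difference. If the coordinators hold that role, comparative results reach people involved in running the trial while patients are still being followed.

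What is at stake is operational bias. A visible trend can alter how the trial is conducted, for example effort on retention or adherence, or decisions to amend the protocol. If those who see it also treat or assess patients, it can colour judgements too. Deaths and admissions count as progression only if they are attributed to Chagas heart disease, and the secondary ECG and echocardiographic findings also need attribution. LVEF by Simpson's rule leaves less room for judgement but still depends on the reader. There is one centre, so no other site could dilute such an effect.

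**Working it through.** The plan gives no figure to reproduce. The check sets its statements side by side.

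**Step 1. Which triggers need a by-arm comparison?**

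| Trigger | Can it be assessed on pooled, blinded data? |
|---|---|
| 10% difference in LVEF among groups | No, it is a between-arm contrast |
| 50% reduction in progression (read as treated against control) | No, between-arm contrast |
| Increase of 10% or more in severe adverse events in one group | No, between-arm contrast |
| Serious adverse events in at least 5% of volunteers | Yes, worded as an overall proportion |

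Three of the four need the comparison, and the article attaches a significance level of 0.01 or less to the estimates.

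**Step 2. Who may act on them?** The text gives the initiating role to either the DSMB or the coordinators and does not confine the coordinators to the pooled trigger. For the other three, a coordinator-initiated stop is possible only if the coordinators have seen the comparison.

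**Step 3. Do other statements agree?** Interim analyses are submitted to the DSMB, so they are prepared outside it. Under Ethical considerations, the DSMB confirms a protocol change that follows from between-group differences. Both fit a flow in which comparative results exist outside the DSMB first. Neither proves who holds them.

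**Step 4. Is anything stated that would contain this?** The Blinding section covers patients, care providers and assessors but is silent on coordinators. Study design and settings lists the unit's staff without mentioning coordinators. The article nowhere says whether coordinators also treat or assess patients, or whether interim results are coded.

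**Step 5. How much of the trial follows the looks?** Follow-up is 60 months. From the Outcomes section, the post-baseline echocardiograms fall at 6, 12, 24, 36, 48 and 60 months. For the last volunteer:

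| Look (month) | Follow-up remaining | Echocardiograms remaining |
|---|---|---|
| 6 | 60 − 6 = 54 months | 5 of 6 |
| 18 | 60 − 18 = 42 months | 4 of 6 |
| 30 | 60 − 30 = 30 months | 3 of 6 |
| 42 | 60 − 42 = 18 months | 2 of 6 |

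These are upper limits, because volunteers enrolled earlier have less follow-up left at each look.

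**The case against.** **The blinding is not shown to fail.** A reader might infer that the coordinators' role breaks the stated blinding, or contradicts the sentence about the single pharmacist. The document does not support that. Coordinators appear in neither list of blinded people, and they are not said to treat or assess patients. The pharmacist sentence concerns the contents of individual boxes, which an arm-level table does not disclose. The table could also be coded: the Randomization section has the pharmacist settle by coin flip which group is placebo. This objection stands and limits the point to a risk. Coding would reduce the risk but not remove it, since the direction of a difference invites guesses about which arm is selenium.

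**The coordinators may not need comparative data.** Interruption is framed as ethical, one trigger is pooled, an independent statistician could be the preparer, and every route passes through the external DSMB. This stands in part. It shows that the role could be used blind for one trigger, but not for the other three, and the DSMB's confirmation comes after the coordinators have acted.

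**Access rules belong in a charter or the full protocol.** That is true of who prepares reports and how they are coded, and silence on those details is not the point here. The point is a rule the article does state. A charter confining by-arm results to the DSMB would leave the coordinators unable to use the published rule on three of its four triggers, so the two would conflict.

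**The size of any bias is unknown.** This stands. The document offers no basis for assuming a particular shift in outcome classification. Assessment is stated to be blinded, echocardiograms are stored digitally, and the main analysis is longitudinal LVEF modelling, so only part of the outcome set rests on attribution.

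**Conclusion.** The point holds as a weakness in how interim roles are assigned. For three of four triggers, the article gives the coordinators an initiating role that can be exercised only with comparative interim results, at any of four looks. For the last volunteer, up to 54 of 60 months of follow-up come after the first look.

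This rests on reading the progression trigger as a comparison of arms and on taking the coordinators' route to cover every trigger, as the text does. It does not rest on coordinators being clinically involved. The article leaves that open, and the risk to outcome judgement would be greater if they are. No effect on error rates or on the treatment estimate can be derived. The change is inexpensive and worth making. It does not correct a demonstrated failure of blinding.

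**What to change.** Amend Interim analyses and stopping rules, and the matching sentence under Ethical considerations, so that:

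1. By-arm interim results go only to the external DSMB. They are prepared by someone outside trial conduct, or by running a prespecified analysis script with the pharmacist's code list and sending the output directly to the DSMB.
2. Only the DSMB may start a recommendation to stop or alter the trial on a between-arm comparison of efficacy or safety.
3. Coordinators receive only the recommendation (continue, modify or stop). They may start one themselves only on pooled blinded data or external information.
4. The Blinding section states the coordinators' status and agrees with these roles.

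The cost is about one paragraph, since the DSMB and the code-holding pharmacist already exist. The downside is that the coordinators lose sight of interim comparisons. Trial status says recruitment is still open and the first look comes 6 months after the last enrolment, so at the time of the article the change could precede every look.

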## Methods/design

### Ethical considerations

The trial was approved by the Evandro Chagas National Institute of Infectious Diseases (INI) Research Ethics Committee (CEP-INI, CAAE 0043.0.009.000-04) and conforms to standards currently applied by the Brazilian National Committee for Research Ethics (CONEP). An external data safety monitoring board (DSMB) will monitor this trial to guarantee the quality of the study. The trial protocol may be altered, with confirmation from the DSMB, if interim analyses demonstrate statistically significant differences in the primary end point between groups. If significant beneficial effects of Se supplementation are found, Se treatment will be offered to those patients who were randomized to the placebo group.

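### Four interim looks at p≤0.01 are not allowed for in the α of 0.05 used to size the trial, and a second interim trigger in Ethical considerations has no stated level.

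*Protocol article*

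**What the plan says.** Three places in the protocol article bear on this point.

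- **Sample size and Table 1.** The text reads "we considered an α error of 0.05, a β error of 0.20", and the table footnote repeats it: "Estimate was calculated with an α error of 0.05, a β error of 0.20 and progression rates in 5 years". The inputs are 5-year progression of 54% on placebo and 27% on selenium, with 65 patients per arm. Interim looks are not mentioned.
- **Interim analyses and stopping rules.** Four analyses are planned, when the last volunteer reaches 6, 18, 30 and 42 months. Stopping may be recommended for positive or negative results. The efficacy conditions are a 10% difference in LVEF or a reduction in progression of at least 50%, and in either case "All these estimates should have a significance level of 0.01 or less in any of the interim analyses".
- **Ethical considerations.** The protocol may be altered, with confirmation from the monitoring board, "if interim analyses demonstrate statistically significant differences in the primary end point between groups". If significant benefit is found, placebo patients will be offered selenium. No level, effect size or link to the stopping rule is given.

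The Statistical analysis section names no significance level for the final analysis.

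**The concern.** A flat 0.01 at four looks uses an appreciable part of a 5% error budget. If the final test is then made at the full 0.05, the chance of a false claim at some point exceeds the level used to size the trial. Only a lower final level or stricter interim levels would prevent this, and the article states neither.

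The second issue is that the article has two interim triggers. An interim result with p = 0.03, or with p = 0.005 and a 40% reduction in progression, could be called statistically significant under Ethical considerations, yet would not meet the stopping rule. Offering selenium to the placebo group would end the randomized comparison, so it matters which trigger the monitoring board applies.

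**Working it through.** **1. The plan's own figure.** Table 1 gives p₁ = 0.54, p₂ = 0.27, difference 0.27, mean 0.405. Two-sided α 0.05 is assumed because sidedness is not stated.

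n = [1.960·√(2·0.405·0.595) + 0.842·√(0.54·0.46 + 0.27·0.73)]² / 0.27² = 50.7, so 51 per arm. With continuity correction it is 57.9, so 58 per arm.

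The stated 65 is not reached from the stated inputs alone. One route is 58/0.9 = 64.4, rounded up to 65, which needs an unstated 10% dropout. Power at 65 per arm is 88.9% by the uncorrected formula. None of this affects the α result. It shows only that the calculation is a fixed-sample one at 0.05.

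**2. Type I error without size conditions.** The interim critical value is |Z| ≥ 2.576 at each of four looks, and the final one is |Z| ≥ 1.960. The correlation between looks i < j is √(tᵢ/tⱼ), where t is the information fraction. The article gives no information fractions, so they are assumed. The joint normal distribution was integrated numerically.

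| Information at the five analyses | Spent at interims | Total, final at 0.05 | Final level that restores 0.05 | Total if 0.05 at all five |
|---|---|---|---|---|
| 0.1, 0.3, 0.5, 0.7, 1 (months/60) | 0.031 | 0.069 | 0.028 | 0.156 |
| 0.2, 0.4, 0.6, 0.8, 1 | 0.029 | 0.065 | 0.033 | 0.142 |
| 0.4, 0.55, 0.7, 0.85, 1 | 0.025 | 0.060 | 0.039 | 0.121 |
| 0.6, 0.7, 0.8, 0.9, 1 | 0.021 | 0.055 | 0.044 | 0.103 |

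The looks are timed on the last volunteer, so earlier entrants have longer follow-up. Information in proportion to months/60 is therefore a reasonable early limit. A still earlier pattern (0.05, 0.2, 0.4, 0.6, 1) gives 0.0725. The simple sum 4 × 0.01 + 0.05 = 0.09 is an upper bound.

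**3. Progression with the size condition.** Null trials were simulated with 65 per arm, a constant hazard, looks at 6, 18, 30 and 42 months, and a final test at 60 months. An interim stop needs p ≤ 0.01 and a risk ratio of at most 0.5.

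| 5-year rate, both arms | Final test alone | Stops in both directions | Benefit stops only |
|---|---|---|---|
| 14% | 0.048 | 0.055 | 0.051 |
| 27% | 0.052 | 0.064 | 0.058 |
| 40% | 0.052 | 0.067 | 0.060 |
| 54% | 0.046 | 0.063 | 0.054 |

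The final test alone differs from 0.05 because the counts are discrete.

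**4. LVEF with the size condition.** The article gives no SD, so 8 to 15 ejection-fraction points is assumed. The standard error of the difference is SD·√(2/65), which is 1.40 to 2.63 points.

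- If 10% means 10 points, the condition requires |Z| ≥ 10/1.40 = 7.1 to 10/2.63 = 3.8. The interims then spend almost nothing, and the total is about 0.050.
- If it means about 5 points (a relative 10% of an assumed LVEF of 50%), the condition requires |Z| ≥ 3.6 at SD 8. At SD 12 or more it no longer binds beyond 2.576. The total runs from 0.050 to 0.071.

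**5. The second trigger.** Ethical considerations states no level. If the 0.05 of the sample-size section were applied at every look, the last column of the first table applies: 0.10 to 0.16.

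**6. Check of the remedy.** Interims at 0.001 and a final test at 0.049 give 0.049 to 0.0505 over the same four patterns.

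**The case against.** The strongest reply has four parts.

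- **The final level is not stated.** The 0.05 is a sample-size input, and an analysis plan that is not shown may set a lower final level. This stands. A reader might infer that the article fixes an unadjusted final test at 0.05, but it does not say so. What it does fix is 0.01 at four looks beside a calculation at 0.05 with no allowance for them.
- **The size conditions limit the inflation.** This stands in part. For LVEF, the subject of the main analysis, a 10-point threshold removes the inflation. The article does not say whether points or a relative change is meant. For progression, the 50% condition leaves a total of up to about 0.06 counting benefit stops only.
- **Larger figures do not follow from the stopping rule.** A reader might infer a false-positive rate above 0.10 by adding the two main outcomes together, or by calling the second trigger looser as a fact. The first ignores the size conditions and brings in a separate multiplicity question. The second rests on reading an unspecified level as 0.05, when the wording could also be a loose summary of the 0.01 rule.
- **Both rules are discretionary.** Altering the protocol and stopping the trial are each worded as permitted and involve the monitoring board, so the two sections do not strictly compel opposite actions. This stands. The mismatch in criteria remains, and an analysis plan would not remove it from the article.

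**Conclusion.** The concern holds in a limited form. The sizing α of 0.05 is not protected by the interim rule as written. If the final test is at 0.05, the excess is at most about 2 percentage points without size conditions (0.069 − 0.05 = 0.019). It is about 1 point or less for benefit stops on progression, and about nil for LVEF on the 10-point reading. These figures assume two-sided tests and the information fractions shown. The LVEF figures also assume the SD range, and the progression figures a constant hazard.

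The mismatch between Ethical considerations and the stopping rule needs no such assumptions, because the two sections give different interim criteria for action on the same data. The 0.10 to 0.16 shows what is at stake if the undefined trigger is read as 0.05. It is not a property of the stopping rule itself.

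**What to change.** Reconcile the two sections so that both cite one efficacy boundary, and state the final level that goes with it. Two options keep the overall level at about 0.05:

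1. Interim efficacy at two-sided p ≤ 0.001 and a final test at 0.049.
2. Interim efficacy kept at 0.01, with the final level lowered to about 0.028 to 0.044 according to the actual information fractions.

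Also state whether the LVEF threshold is in ejection-fraction points or relative, since this decides whether it limits the inflation.

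The change is one of wording. Option 1 makes early stopping for benefit harder and costs almost no final power. By the formula in the working, power at 65 per arm goes from 88.9% at 0.05 to 88.8% at 0.049. Option 2 costs somewhat more at the final test: 87.8% at 0.044 (critical value 2.014) and 83.5% at 0.028 (critical value 2.197), both still above the planned 80%. These powers assume the Table 1 rates and no dropout. Recruitment was still open, and the first interim waits until the last volunteer reaches 6 months, so under the plan the change can be made before any comparison of the groups.

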## Discussion

This clinical trial presents a possible new therapy based on the regulation of inflammation and fibrosis with the potential of delaying the progression of cardiopathy in patients with chronic Chagas heart disease. If the hypothesis is confirmed, it will constitute a new contribution to the improvement of the health care of the affected population, with prospective application in all of Latin America, where the WHO registers the existence of about 10 million infected people [48], and 30% of them (3 million to 4 million people) are expected to develop the cardiac form. Supplementation with micronutrients is simple and has been widely employed by oral administration [49]. In many countries, including the United States and France, Se is considered a supplement instead of a medicine. According to the Brazilian Agency of Sanitary Inspection, 100 μg of Se is considered medicinal because it is up to 100% of the recommended 34-μg daily intake. However, the daily level in our trial is within the limits considered safe (150 μg maximum; Secretariat of Health Surveillance, Ministry of Health (SVS/MS) Ordinance 40/1998). The inorganic form of Se (sodium selenite) was chosen because it has been shown to prevent Keshan cardiopathy, to reduce electroechocardiographic alterations in patients nourished by the parenteral route and to reduce reinfarction and cardiac death due to acute myocardial infarction [50–52]. Because Chagas heart disease progresses slowly (1% to 3% per year) [5], this clinical trial will last 5 years. This duration is short compared to the natural progression rate of this disease. If Se treatment turns out to be beneficial in this trial, a new and affordable treatment strategy for Chagas heart disease will be readily available for people with chronic *T. cruzi* infection all over the world.

